## Abstract

**Background:**

The only subgroups of patients with heart failure and atrial fibrillation in which the efficacy of cardiac resynchronization therapy has been scientifically proven are patients with indications for right ventricular pacing and patients after atrioventricular junction ablation. However it is unlikely that atrioventricular junction ablation would be a standard procedure in the majority of the heart failure patients with cardiac resynchronization therapy and concomitant atrial fibrillation due to the irreversible character of the procedure and a spontaneous sinus rhythm resumption that occurs in about 10% of these patients.

**Methods/Design:**

Pilot-CRAfT is the first randomized controlled trial evaluating the efficacy of a rhythm control strategy in atrial fibrillation patients with cardiac resynchronization therapy devices. The aim of this prospective, single center randomized controlled pilot study is to answer the question whether the patients with cardiac resynchronization therapy and permanent atrial fibrillation would benefit from a strategy to restore and maintain sinus rhythm (that is ‘rhythm control’ strategy) in comparison to rate control strategy. The study population consists of 60 patients with heart failure and concomitant long-standing persistent or permanent atrial fibrillation who underwent a cardiac resynchronization therapy device implantation at least 3 months before qualification. Study participants are randomly assigned to the rhythm control strategy (including electrical cardioversion and pharmacotherapy) or to the rate control group whose goal is to control ventricular rate. The follow-up time is 12 months. The primary endpoint is the ratio of effectively captured biventricular beats. The secondary endpoints include peak oxygen consumption, six-minute walk test distance, heart failure symptom escalation, reverse remodelling of the heart on echo and quality of life.

**Trial registration:**

NCT01850277 registered on 22 April 2013 (ClinicalTrails.gov)

## Background

The heart failure (HF) patients with concomitant atrial fibrillation (AF) make up a significant subgroup of patients eligible for cardiac resynchronization therapy (CRT) but their treatment remains problematic.

The prevalence of AF as well as chronic HF is significant and it is still growing. It has been estimated that 1 to 2% of population suffers from AF - the most common form of sustained arrhythmia [1]. The prevalence of HF in general population is 1 to 2% and rises with age, reaching >10% in a subpopulation of subjects aged 70 years or older [2]. The coexistence of AF and HF is very frequent. Both illnesses may negatively influence and promote each other [1]. The coexistence of AF in HF patients is related to the severity of heart failure. The prevalence of AF in New York Heart Association (NYHA) class I is about 5%, reaching 25 to 50% in NYHA III/IV subgroups [3, 4]. About 23% of patients undergoing a CRT device implantation in Europe have AF [5]. With population ageing, estimated growth in the prevalence of AF and HF and broad label of CRT implantation, the issue of proper treatment of CRT patients with AF becomes crucial.

Nevertheless, the CRT in patients with AF encounters many problems and its beneficial effect in this group of patients is not fully established. The indications for CRT arise from the evidence coming from the studies where AF patients were absent or barely present. The only subgroup of patients with AF in which beneficial effect of CRT is scientifically proven (that is proven in randomized controlled trails (RCTs)) are the patients with concomitant indications for right ventricular pacing [6, 7]. As a result, the present indications for the CRT in patients with concomitant AF stem from the recommendations for those in sinus rhythm (SR), having a level of evidence C in IIb class [2]. Moreover, there is no sufficient data evaluating the CRT impact on mortality in the AF patients and an emphasis is put on the lack of trials comparing the rhythm control versus rate control strategy in this group of patients [2, 5].

Contrary to the widening range of patients with HF suitable for CRT, the evidence is growing that the benefit of resynchronization in the subgroup of patients with AF is reduced. The initial meta-analyses of the studies comparing the efficacy of CRT in patients with AF versus SR suggested similar effect of response to CRT in the AF group in terms of NYHA functional class or ejection fraction and lower effect on the exercise tolerance improvement measured by means of six-minute walk test (6MWT) [8, 9]. The recent and larger meta-analysis has shown however, that the patients with AF have higher mortality and higher rate of non-response to CRT than their SR counterparts [10]. Whatever the results of those systematic reviews, it should be mentioned that the vast majority of the data included in those analysis has been derived from observational studies - not randomized trials, which are not available.

The lower effectiveness of CRT in AF patients is explained by the irregular and unpredictable character of ventricular beats in this arrhythmia which lowers the ratio of effectively biventricular paced captured beats (BiVp%). This hypothesis is corroborated by studies of AF patients on CRT undergoing atrioventricular junction ablation (AVJA), which enables the BiVp% to be close to 100%. According to the registries, the CRT efficacy in patients with AF undergoing AVJA is similar to that in patients in SR, whereas the patients with AF but no AVJA seem not to benefit from resynchronization at all, even if BiVp% exceeds 85% [3, 11]. As a result, the estimated BiVp% that guarantees the CRT efficacy is ≥95% [11] or even ≥98 to 99% [5, 12, 13]. The most recent ESC guidelines put an emphasis on the achievement of biventricular capture as close as possible to 100% and - unless achieved - on performing AVJA [5]. Nevertheless, the significant group of AF patients with already-implanted CRT devices present with this goal not sufficiently met.

Although AVJA seems to provide the efficacy of CRT [2, 5, 7, 14], it is unlikely that performing an iatrogenic III° atrioventricular block will be recommended in all patients with AF undergoing CRT implantation. Such an approach would generate an enormous group of pacemaker-dependent patients - a potentially dangerous situation. Moreover, performing an AVJA seems questionable, bearing in mind the spontaneous SR resumption that occurs in 10 to 25% of the CRT patients with permanent/long-standing persistent AF [15, 16]. This phenomenon may occur even a few years after the implantation of CRT device [16]. Due to the limitations of the AVJA, the strategy of SR resumption and its maintenance seems to be a reasonable option in the group of CRT patients with AF.

To the authors’ best of knowledge, a randomized, prospective trial assessing the influence of rhythm control strategy on CRT efficacy in AF patients has not yet been performed. The only trial upon this issue was the non-randomized, cohort study of Turco *et al*. [17], which has shown a positive effect on end-diastolic volume in the rhythm control group, whereas the influence on ejection fraction was comparable between the rhythm and the rate control groups.

The promising results of the rhythm control strategy were also achieved in the PABA-CHF trial which compared pulmonary vein isolation (PVI) versus the *ablate and pace* strategy (that is performing an AVJA + CRT-D (CRT with defibrillator function) implantation) in HF patients with paroxysmal or persistent/permanent AF [18]. During the 6-month observation the patients who underwent PVI had longer 6MWT distance, higher ejection fraction and they claimed better quality of life. The effect was even more profound in the permanent/persistent AF subgroup. The trial did not prove any favorable impact of rhythm control strategy on mortality and showed a higher hospitalization rate in this group; however, it analyzed the overall group HF and AF patients, not the subgroup meeting the current CRT-D implantation criteria and compared the PVI alone (that is not combined with CRT) has in comparison to the patients treated with CRT + AVJA.

## Methods/Design

### The aim of the study

The aim of the study is to answer the question whether the patients with permanent or long-standing persistent AF on cardiac resynchronization therapy due to heart failure will benefit from the treatment strategy to resume and maintain sinus rhythm in terms of achievement of adequate BiVp%. An additional goal of the study is the identification of potential factors predicting the efficacy/the lack of benefit of the rhythm control strategy. As it is a pilot study, its other goal is to collect data which would enable the authors to design another, larger study, which would have a power to examine the influence of a rhythm control strategy versus rate control strategy on the mortality and morbidity of HF in this group of patients.

### Study scheme

The Pilot-CRAfT study is a single-center, open, prospective, randomized controlled trial. The trial enrolls 60 patients with HF and concomitant permanent or long-standing persistent AF who underwent CRT implantation at least three months before the enrollment in the Second Department of Coronary Artery Disease of the Institute of Cardiology in Warsaw, Poland. The inclusion and exclusion criteria are listed in the Table 1. Before the enrollment each participant will give written, informed consent.

**Table 1 Tab1:** **The inclusion and the exclusion criteria for the Pilot-CRAfT study**

Inclusion criteria:	
1)	Permanent or long-standing persistent AF (definitions according to the latest ESC guidelines on AF)
2)	At least three months after the procedure of a CRT device implantation
3)	A CRT device with the presence of a right atrial electrode
4)	Age: ≥18 years old
5)	Effectively biventricular paced captured beats percentage <95%
6)	Effective therapy with oral anticoagulants for at least three weeks
7)	Written informed consent
Exclusion criteria:	
1)	Reversible causes of AF
2)	Significant valve disease
3)	Advanced AV block (including: AVJA)
4)	Contraindications to amiodarone (hyperthyroidism, non-compensated hypothyroidism, drug intolerance, QT >460 ms for men, QT >450 ms for women)
5)	Long-QT syndrome
6)	Cardiac transplantation in six months
7)	Life expectancy less than one year
8)	LA diameter larger than 6 cm
9)	Heart failure decompensation within 48 hours before the qualification
10)	Chronic dialysis
11)	History of alcohol abuse
12)	Pregnancy or lack of effective contraceptive therapy (in case of females in the reproductive age)
13)	Participation in other clinical trial

AF, atrial fibrillation; AV, atrioventricular; AVJA, atrioventricular junction ablation; CRT, cardiac resynchronization therapy; ESC, European Society of Cardiology; LA, left atrium.

### Principles of the management of the patients (treatment strategies)

The enrolled patients are randomly assigned to one of the two groups (in a 1:1 ratio). In the first group, a strategy to restore and maintain SR is implemented (that is rhythm control strategy - the active treatment group). In the second group, a strategy to slow ventricular rate will be implemented (that is rate control strategy - the control group).

#### Rhythm control group

The basic method to restore and maintain sinus rhythm comprises a combination of pharmacological antiarrhythmic treatment and external electrical cardioversion (EEC). The attempts to restore SR must not be performed unless the patient has been treated effectively with oral anticoagulants for at least three weeks.

The pharmacological treatment consists of amiodarone administered orally. The loading dose of amiodarone is up to 600 mg daily for the first 4 weeks. Then, a maintenance dose of 200 mg/daily is administered (a dose may be adjusted at discretion of treating physician). The loading dose may be modified or omitted, especially, if a patient had been given amiodarone before the enrollment. If any contraindications to amiodarone occur during the treatment, it must be discontinued promptly. The use of other antiarrhythmic agents is possible unless they are contraindicated.

A basic tool to restore SR in the trial is an EEC. The first EEC should be performed after the complete loading dose of amiodarone has been administered (unless SR is restored spontaneously). Up to three shocks during one cardioversion are allowed. The amount of the energy delivered is left to discretion of a physician performing the EEC. If AF recurs, the patient should undergo the next EEC as soon as possible but preserving the safety time margins of effective anticoagulation period (at least three weeks). The maximal number of EEC procedures is three and the third one is possible only if AF recurs no earlier than three weeks after the second EEC and SR resumption is related to alleviation of HF symptoms. If SR resumption or its maintenance is impossible or AF recurs after the third EEC, a strategy of *rhythm control* is discontinued and a *rate control* strategy is implemented.

In patients undergoing the *rhythm control strategy* treatment, a procedure of ablation of AF substrate (that is PVI) is possible. The decision to offer the patient an ablation must be made collectively at the discretion of the therapeutic team. Routinely in the trial, a PVI procedure is allowed and offered to patients responding to EEC after the second recurrence of AF.

#### Rate control group - control group

The treatment goal in the *rate control* group (that is the control group) is to slow and control ventricular rate by means of pharmacological antiarrhythmic agents and AVJA as to achieve satisfactory BiVp%. The pharmacotherapy should include negative chronotropes and negative dromotropic drugs such as beta-blockers, digitalis and amiodarone (the use of other, less popular agents, is also possible). It should be consistent with the current guidelines of treatment of HF and AF. The choice of the agents and its’ dosage is left to discretion of the treating physician. An AVJA procedure in this group of patients is possible but not obligatory. The decision to perform AVJA is left to the discretion of the treating physician. An effective anticoagulant treatment is essential in both groups.

### Follow-up

The follow-up period is 12 months. The patients are scheduled for control visits every three months. Every control visit consists of: a standard review of a device and treatment; an assessment of the actual BiVp%; the questions concerning the occurrence of the analyzed endpoints and a standard 12-lead ECG. Additionally, on the qualification visit, and control visits after 3 and 12 months, a 6MWT, an echocardiograph and a cardiopulmonary exercise test (CPX) are performed and the patients are asked to fill the questionnaire about their quality of live, that is the Minnesota Living with Heart Failure Questionnaire (MLHFQ), © University of Minnesota [19, 20], (MLHF contact information and permission to use: MAPI Research Trust, Lyon, France. Email: [contact] - Internet: http://www.mapi-trust.org and University of Minnesota. Email: [contact] - Internet http://www.mlhfq.org). Moreover, a thyroid-stimulating hormone (TSH) level control is performed on the qualification visit and during visits after six and twelve months.

### Endpoints

All of the endpoints will be assessed in two timeframes: at three months and one year from the baseline examination timeframe.

The primary endpoint is an overall BiVp% during the one-year study period (that is a mean BiVp% through the whole follow-up period). The ‘triggered’ paced beats are not treated as effective and are excluded from the analysis.

The secondary endpoints are listed in the Table 2.

**Table 2 Tab2:** **Secondary endpoints of the Pilot-CRAfT trial**

	Secondary endpoints:
BiVp%:	
•	BiVp% change from baseline.
Physical competence:	
•	6MWT distance
•	Peak oxygen uptake (peak VO_2_) in CPX
•	NYHA functional class
The echocardiographic assessment of the reverse remodelling:	
•	Increase in left ventricle ejection fraction (LVEF)
•	Decrease in left ventricle diastolic diameter and volume (LVEDD, LVEDV)
•	Decrease in left ventricle systolic diameter and volume (LVESD, LVESV),
•	Decrease in size of the left atrium (LA)
•	Decrease of the severity of mitral insufficiency
Quality of life:	
•	Measured with the Minnesota Living with Heart Failure Questionnaire
Clinical endpoints:	
•	Unplanned hospitalizations due to heart failure exacerbations
•	Death
•	Cardiovascular death
•	Hospitalizations due to cardiovascular causes
•	Stroke/TIA
•	A combined endpoint including unplanned hospitalizations due to cardiovascular causes or death
Heart arrhythmias:	
•	AF - using *mode switch* to measure time of AF with fast ventricular rate
•	Ventricular tachycardia including *torsade de pointes* tachycardia and ventricular fibrillation
In the CRT-D subgroup:	
•	Number of adequate and inadequate shocks (separately)
•	The prevalence of electrical storm
Adverse events:	
•	Pharmacotherapy related
•	Device related
•	Cardioversion related
•	AVJA related

The clinical endpoints, the occurrence of heart arrhythmias and adverse events are collected for safety measures. All of the endpoints will be assessed at three-months and one-year from the baseline timeframes.

6MWT, six-minute walk test; AF, atrial fibrillation; AVJA, atrioventricular junction ablation; BiVp%, effectively biventricular paced captured beats percentage; CPX, cardiopulmonary exercise test; CRT-D, cardiac resynchronization therapy with defibrillator function; TIA, transient ischemic attack.

Based on the results of the primary endpoint, the authors plan to perform a preliminary identification of the factors predicting the response to the *rhythm control* strategy.

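### Table 2 gives cardioversion and AV-junction ablation their own adverse-event categories but gives none to PVI, so procedural harm of the rhythm strategy is under-captured

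*Protocol article*

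**What the plan says.** The Endpoints section refers the reader to Table 2 for the secondary endpoints. The adverse-event block of that table has four lines: "Pharmacotherapy related", device related, "Cardioversion related" and AVJA related. It contains no line for PVI, for ablation in general or for other procedures. The note under the table gives the purpose: "The clinical endpoints, the occurrence of heart arrhythmias and adverse events are collected for safety measures".

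The Rhythm control group section says that in this arm "a procedure of ablation of AF substrate (that is PVI) is possible", by collective decision of the therapeutic team, and adds: "Routinely in the trial, a PVI procedure is allowed and offered to patients responding to EEC after the second recurrence of AF".

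The Rate control group section sets the goal of slowing the ventricular rate "by means of pharmacological antiarrhythmic agents and AVJA as to achieve satisfactory BiVp", and states: "An AVJA procedure in this group of patients is possible but not obligatory". It does not mention PVI.

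**The concern.** The table does more than promise that adverse events will be recorded. It names categories procedure by procedure, and it leaves out a procedure that the treatment section provides for. The optional ablation of the control strategy has its own line for complications; the ablation offered under the experimental strategy has none.

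The list also appears to shape data collection, because the Follow-up section has each control visit include questions about the analyzed endpoints. What is not an endpoint is less likely to be asked about.

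The stake is the usefulness of the pilot. Its stated aims include supplying data for a larger trial on mortality and morbidity, and the Discussion hopes to establish rhythm control as an alternative to rate control. A safety summary in which one invasive component of the rhythm strategy has no line of its own would tend to make that strategy look somewhat safer than it is. The Background itself reports a higher hospitalization rate with rhythm control in the cited trial that compared PVI with AVJA plus resynchronization.

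**Working it through.** No figure in the plan bears on this point, so there is none to reproduce. The check compares the procedures allowed with the categories provided.

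**Step 1. Procedures against categories**

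| Procedure | Where provided for | Who can receive it | Own line in Table 2? |
|---|---|---|---|
| EEC | Rhythm control group | Rhythm arm, at most three procedures | Yes |
| PVI | Rhythm control group | Rhythm arm; team decision, with a routine offer to EEC responders after the second recurrence | No |
| AVJA | Rate control group; Device control | Control arm, optional; also open to rhythm-arm patients who switch to rate control | Yes |

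PVI is the only one of the three without a line.

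**Step 2. Where a PVI complication would be recorded if Table 2 is followed as written**

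- If it leads to death, stroke/TIA, a cardiovascular hospitalization or a listed ventricular arrhythmia, it is counted there, but nothing marks it as caused by PVI.
- If it is none of these, it has no named endpoint, unless it happens also to qualify as a drug or device event.
- An AVJA complication of the same severity would be counted and attributed in either case.

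**Step 3. How many patients this could concern**

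The document gives no expected number of PVI procedures. The only related rates are those in the Discussion from the cited non-randomized cohort: sinus rhythm restored in 82% after a single cardioversion, and maintained for a year in about 60%. The denominator of the 60% is unclear, so both readings are shown for the 30 planned rhythm-arm patients.

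- If 60% is of those converted, relapse among the converted is 1 − 0.60 = 0.40. First recurrences: 30 × 0.82 × 0.40 = 9.8. Second recurrences: 30 × (0.82 × 0.40)² = 30 × 0.328² = 3.2.
- If 60% is of all patients, relapse among the converted is (82 − 60)/82 = 22/82 = 0.27. First recurrences: 30 × 0.22 = 6.6. Second recurrences: 30 × 0.22² = 1.5.

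This gives about 1.5 to 3 patients reaching the routine offer. The calculation is only illustrative. It assumes that the second cardioversion has the same success and relapse rates as the first, that every patient is cardioverted again after a first recurrence, and that all of this falls within 12 months. The authors expect better maintenance of sinus rhythm than in that cohort, which would lower the figure. The team may also choose PVI at other times, which would raise it. Not every patient offered PVI would accept.

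**The case against.** The strongest case on the other side has four parts.

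- **The main procedure of the rhythm arm is listed.** The Rhythm control group section calls EEC the basic tool, and "Cardioversion related" is a named category. The line "Pharmacotherapy related" covers amiodarone. A reader might infer from the missing PVI line that procedural harm is counted for the control strategy and omitted for the experimental one. The table does not support that: one second-line procedure is missing.
- **AVJA is not a control-only category.** When rhythm control fails it is replaced by rate control, and the Device control section foresees a decision on AVJA at visits. Under intention to treat, AVJA harm after a switch counts in the rhythm arm. The asymmetry between the arms is therefore less clean than the table suggests.
- **Serious events are partly caught.** A reader might infer that the listed endpoints would show no PVI harm by construction. They would not: death, stroke/TIA and cardiovascular hospitalization are all endpoints, and the table note says the clinical endpoints too are collected for safety.
- **The article may not show everything.** It condenses a full protocol, and the case report form is mentioned but not shown. Table 2 does not say that other adverse events go unrecorded.

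The first three parts stand and limit the claim to under-capture and lack of attribution. The fourth stands in part. Whether the case report form has a PVI field cannot be known from the article, so no claim about actual safety monitoring can be made. But the mismatch is between two statements that are both in the article, an explicit list of causes and the treatment section. It is not a detail that an article merely leaves to another document.

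The Discussion also concedes that the sample serves the primary endpoint only. That lowers the importance of any formal safety comparison, but not the case for recording harms correctly in a pilot.

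**Conclusion.** The point holds in limited form. Table 2 has a named category for EEC and for AVJA complications and none for PVI, although PVI is a routine conditional offer in the rhythm arm and is not mentioned for the control arm. As written, serious PVI complications are partly counted but not attributed, and the remainder have no named endpoint. Procedural harm of the rhythm strategy is under-captured relative to AVJA, in a direction that would favour rhythm control.

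The size cannot be derived from the document and is probably small; the illustration of 1.5 to 3 patients rests on the assumptions set out with it. A reader might take the roughly 40% relapse to mean 12 of 30 patients with a recurrence and a sizeable group receiving PVI. The Discussion does not support that: 30 × 0.40 = 12 treats every patient as converted, and the routine offer requires a second recurrence after a response to EEC.

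The primary endpoint, its analysis and the sample size are unaffected. The conclusion assumes only that Table 2 is meant as the list of adverse-event endpoints, as the Endpoints section indicates.

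**What to change.** Add a 'PVI related' line to the adverse-event block of Table 2, and to the case report form if it does not already have one. Report procedure-related events (EEC, PVI and AVJA) by randomized arm, by type and as a total, so that procedures received after a switch of strategy are counted where the patient was randomized.

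The cost is one extra reporting category. No procedure, visit or treatment rule changes, and the sample size is untouched. The Trial status section gives recruitment as ongoing, so the line can be applied prospectively; PVI events that occurred before the change would have to be classified from existing records.
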